#### 2.8.2. Safety outcomes.

Data on vital signs and relevant laboratory tests including blood routine tests, urine routine tests, liver and kidney function tests, fecal tests, and electrocardiography, will be collected at baseline assessment and on the day of the hCG trigger. The adverse events will be recorded and evaluated at every visit of participants during the study period.

### 2.9. Statistical analysis

#### 2.9.1. Sample size calculation.

##### 2.9.1.1. Sample size calculation

Sample size calculations referred to previous studies, and the clinical outcomes of aged women with POR from the electronic database in our reproductive center.^[9,23]^ The study was designed to detect a difference between groups in terms of 1 additional retrieved oocyte after the hCG trigger with a standard deviation of 3 retrieved oocytes. The power is set at 90%, along with a 2-sided 5% type I error rate. To account for a 20% dropout rate, the sample size of 480 was determined using PASS 15.0 (NCSS, LLC, Kaysville, Utah), in which 240 participants were in each group.

#### 2.9.2. Planned data analysis.

Intention-to-treat (ITT) analysis will be used for baseline comparisons and the assessment of the effect of EZTG on the total number of retrieved oocytes per COS cycle, as well as other secondary outcomes. T-test, Wilcoxon rank-sum test, or chi-square test will be used to test for differences. The results will be given as mean (standard deviation), median (interquartile range), or frequency (percentage) according to the type and distribution of the variables. A 2-sided *P* < .05 is considered statistically significant with a confidence interval of 95%. Per protocol analysis will be conducted as a sensitivity analysis, including those patients who completed their randomized treatment. If the ITT results conflict with the per protocol results, we will interpret the study results according to the outcome of the ITT analysis.

In addition, a subgroup analysis will be performed according to AFC strata (<5 or ≥5) using a similar approach to the primary analysis. Multiple imputations will be used to process missing values in the data of this study. All statistical work will be performed on SPSS version 26.0 software (IBM Corporation, Armonk, NY).

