### 2.6. Randomization, allocation, and blinding

Randomization and allocation will start on day 2 or 3 of the previous menstrual cycle before IVF. Eligible women will be stratified by AFC (<5 or ≥5) and randomized within the 2 strata. All participants will be randomly assigned to either the EZTG group or the placebo group in a 1:1 ratio. Randomization will be completed by software (R 4.0.0, R Foundation for Statistical Computing, Vienna, Austria), and different-sized block groups of 2, 4, 6 will be applied. Random number tables will be provided by statistical professionals not involved in the rest of the study and the number will be sealed into brown envelopes. Then the group allocation will be accomplished by opening envelopes sequentially in the order in which patients were recruited.

A double-blind study design will be applied to enhance the quality of the study evidence. Both medications (EZTG granules and placebo) will be prepared in a manner that they will appear similar in appearance, flavor, and smell. Clinicians and patients will not be able to distinguish the difference between groups. The outcome assessment and data analysis will also be conducted in blinding. When the clinical trial is over, the final blind-break process is performed by authorized researchers.

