### 2.8. Outcomes

#### 2.8.1. Efficacy outcomes.

The primary outcome is the number of oocytes retrieved per COS cycle.

The following secondary outcomes will also be evaluated as secondary outcomes:

Symptom rating scores of kidney qi-yin deficiency syndrome after treatment (The symptom rating scales is shown in Table 3).Difference in rating scores of kidney qi-yin deficiency syndrome before and after treatment.Average daily dose of gonadotropin per COS cycle.Total gonadotropin dose and duration of ovarian stimulation per COS cycle.Cycle cancelation rate per COS cycle. Cycle cancelation is defined as a cycle canceled before obtaining at least 1 viable embryo for any reason.Good quality embryos rate per embryo. A good quality embryo is defined as an embryo that is graded as 6-cell grade 2 (6CII) or better or blastocyst.Embryo implantation rate per embryo, defined as the number of gestation sacs detected divided by the number of embryos transferred.Clinical pregnancy rate per patient, defined as the number of women with identified clinical pregnancies divided by the number of patients randomized to a specific group. Clinical pregnancy is confirmed when 1 or more gestational sacs are detected on transvaginal ultrasound assessment.Early miscarriage rate per patient, defined as the percentage of participants with loss of a diagnosed clinical pregnancy before 12 weeks gestation to the total patients randomized.CLBR per patient, defined as the proportion of deliveries with at least 1 live birth per started cycle or oocyte aspiration, including all fresh and/or frozen embryo transfers until 1 delivery with a live birth or until all embryos were used (within 1 year after randomization).

**Table 3 T3:** Symptom rating scales of kidney qi-yin deficiency syndrome.

Symptoms	Characteristics and severity of the symptoms	Score
The color and quality of the menstruation	The color of the blood is dark red and the quality is thin and watery	5
	The color of the blood is dark red or the quality is thin and watery	3
	Normal color and quality	0
The waist and knees are sour and powerless, or pain in the heels	Severe discomfort that interferes with daily life	6
	Moderate discomfort	4
	Mild discomfort	2
	No obvious discomfort	0
Dizziness and tinnitus	Severe, occurs constantly and interferes with daily life	6
	Moderate, occurs frequently	4
	Mild, occurs occasionally	2
	Not obvious	0
Mental exhaustion	Severe, occurs constantly and interferes with daily life	6

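### The primary analysis leaves out the AFC strata used in randomisation, and the AFC subgroups have no interaction test: a modest loss for the primary test, a larger risk of misreading the subgroups

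*Protocol article*

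**What the plan says.** Section 2.6 fixes the design: "Eligible women will be stratified by AFC (<5 or ≥5) and randomized within the 2 strata", with 1:1 allocation in blocks of 2, 4 and 6.

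Section 2.9.2 names the tests for the primary and secondary outcomes: "T-test, Wilcoxon rank-sum test, or chi-square test will be used to test for differences". No stratified or covariate-adjusted analysis is mentioned. For subgroups, "a subgroup analysis will be performed according to AFC strata (<5 or ≥5) using a similar approach to the primary analysis". The significance threshold is a two-sided 0.05, with no separate rule for subgroups.

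Section 2.9.1.1 sizes the trial on a mean difference: it is to "detect a difference between groups in terms of 1 additional retrieved oocyte after the hCG trigger", "with a standard deviation of 3 retrieved oocytes".

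Section 2.8.1 lists two symptom-score outcomes: the post-treatment score, and "Difference in rating scores of kidney qi-yin deficiency syndrome before and after treatment".

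**The concern.** Stratified randomisation removes chance imbalance in AFC between the arms. A plain two-sample test does not know this. Its standard error still contains the variation between strata, so it is too large for the design. The more AFC predicts oocyte number, the greater the excess. Section 2.4.1 makes a low AFC part of the definition of poor response, so some prediction is to be expected.

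The subgroup plan raises a separate issue. Two-sample tests within each stratum do not ask whether the effect differs between strata. Each stratum has well under the trial's 90% power, so one significant and one non-significant result is a common outcome even when the effect is the same in both. That pattern could be reported as benefit in one AFC group only.

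Two smaller points follow from the same sentence. A rank-sum test does not estimate the mean difference on which the trial is sized. And neither symptom-score comparison, as planned, is adjusted for the baseline score.

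**Working it through.** **Inputs.** Difference 1, SD 3, 90% power, two-sided 5%, 20% dropout and 480 in total (section 2.9.1.1); 1:1 allocation and AFC strata (section 2.6). The Discussion gives the detectable difference as 3 oocytes. I use 1, because it reproduces 480; a difference of 3 would need only about 22 per arm.

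**1. The plan's own figure.** n per arm = 2 × (1.960 + 1.282)² × 3² / 1² = 189.1, so 190. Dividing by 0.8 gives 238 per arm, or 476. The t-based count is 191, which becomes 239 per arm, or 478. The stated 480 reproduces. With 240 × 0.8 = 192 completers per arm, unadjusted power is 90.3% (t) or 90.4% (normal approximation), before any credit for stratification.

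**2. Effect of leaving out the stratum.** Let R² be the share of oocyte variance explained by AFC stratum. The article gives no value, so a range is assumed.

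- Standard error used by the unadjusted test: 3 × √(2/192) = 0.306.
- True standard error under stratified randomisation: 0.306 × √(1 − R²).
- True alpha = 2 × [1 − Φ(1.96/√(1 − R²))].
- Unadjusted power = Φ[(1 − 1.96 × 0.306)/(0.306 × √(1 − R²))].
- Adjusted power = Φ[1/(0.306 × √(1 − R²)) − 1.96].
- Gap between stratum means implied by R² at an equal split: 6 × √R².

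| R² (assumed) | Implied gap, oocytes | True alpha | Unadjusted power | Adjusted power | Gain, points |
|---|---|---|---|---|---|
| 0.02 | 0.85 | 0.048 | 90.65% | 90.97% | 0.3 |
| 0.05 | 1.34 | 0.044 | 90.99% | 91.79% | 0.8 |
| 0.10 | 1.90 | 0.039 | 91.57% | 93.09% | 1.5 |
| 0.20 | 2.68 | 0.028 | 92.79% | 95.46% | 2.7 |

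A slightly different approximation puts the range of gains at 0.2 to 2.6 points; the difference is immaterial.

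**3. Separate tests in the two strata.** Assume a true effect of 1 oocyte and SD 3 in both strata, with 192 completers per arm.

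- Equal split (96 per arm in each stratum): power is 63% in each. Exactly one significant: 2 × 0.632 × 0.368 = 0.465, about 47%.
- 30:70 split: power is 43% and 78%. Exactly one significant: 0.43 × 0.22 + 0.78 × 0.57 = 0.54.
- No effect in either stratum: at least one significant in 1 − 0.95² = 9.75%.

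The AFC split is not given, so both splits are assumptions. If the stratum explained 20% of the variance, the within-stratum SD would be 3 × √0.8 = 2.68. The chance that exactly one stratum is significant would then be about 40% (equal split) and 49% (30:70), so the conclusion does not depend on SD 3 holding exactly.

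**4. Symptom score.** Take equal variance before and after treatment, and let r be the correlation between the two scores. Relative to the post-treatment comparison (1), the change score has variance 2(1 − r), and the baseline-adjusted comparison has 1 − r².

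| r (assumed) | Better planned comparison | Adjusted | Saving |
|---|---|---|---|
| 0.2 | 1.00 (post-treatment) | 0.96 | 4% |
| 0.5 | 1.00 (either) | 0.75 | 25% |
| 0.8 | 0.40 (change) | 0.36 | 10% |

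**The case against.** The strongest reply is that nothing here is broken. The unadjusted test is valid and meets the planned power. Leaving out a stratification factor makes the test conservative, so it cannot inflate false positives. Much of this detail also commonly sits in an analysis plan that is not shown. That stands as a limit on weight. It does not remove the point, because the article does name its tests and they do not follow its own randomisation.

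Several stronger readings are tempting, and the article does not support them:

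- A reader might infer that adjusting for AFC lifts power from 90% to 93–95%, or is worth 11–25% more patients. For the stratum this uses the wrong comparator. Stratification already raises the true power of the unadjusted test above 90%, and with balanced strata only the estimated standard error changes.
- A reader might infer that the t-test or Wilcoxon test will be chosen from the observed data. The wording about type and distribution in section 2.9.2 governs how results are summarised; no rule for choosing a test is written.
- A reader might infer that the plan will claim a differential effect by comparing P values. It says only that a similar approach is used, and the Discussion itself warns of error in subgroups. Separate testing is the natural reading, but the harm arises only if the results are misread.
- A 25% variance saving for the symptom score holds only at r = 0.5, where the gain over the better planned comparison is greatest.

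It is also fair to say that a large R² is not assured. Eligibility already narrows ovarian reserve or previous yield for many women, and an R² of 0.20 would need stratum means 2.7 oocytes apart.

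**Conclusion.** The point holds as a modest recommendation. The article randomises within AFC strata, names only tests that leave the strata out, and names no test of whether the effect differs by AFC.

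For the primary outcome the loss is small, and its size rests wholly on the assumed R². At the lower end it is negligible. The result would not be wrong, only somewhat less precise than the design allows.

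The subgroup issue is the weightier part and needs no R². With identical effects, discordant stratum results would occur in roughly half of trials under the splits considered. Without an interaction test, the planned analysis offers no formal way to tell such discordance from a real difference.

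The symptom-score point is secondary, and its size varies with a correlation that the article does not give.

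**What to change.** - **Primary analysis:** a linear model of oocyte number on treatment and AFC stratum, reporting the adjusted mean difference with its 95% confidence interval. This is the quantity the trial is sized on. Use a stratified Wilcoxon (van Elteren) test as a sensitivity analysis.
- **AFC subgroups:** a treatment-by-AFC interaction test, with the estimate and confidence interval in each stratum. This holds the chance of a false claim of a differential effect at 5%. State that the test has limited power: at an equal split with SD 3, about 37% for a between-stratum difference in effect of 1 oocyte and 90% for a difference of 2. A non-significant interaction therefore does not show that the effects are equal.
- **Symptom score:** adjust the post-treatment score for its baseline value. Whether the change score is also reported is a matter of choice.
- **Optional:** terms for age and centre. Neither is a randomisation stratum.

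The cost is analysis wording only, ideally settled before unblinding. AFC is known at randomisation, and the before-after outcome already requires a baseline symptom score. Sample size, procedures and data collection are unchanged.

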#### 2.7.4. Embryo transfer and luteal phase support (LPS).

All patients received cleavage-stage embryo transfer on day 3 after oocyte retrieval, or blastocyst transfer on day 5, except for the following cases: uterine or endometrial abnormalities, such as endometriosis, uterine fibroids, endometrial polyps or intrauterine adhesions; serum *P* > 1.5 ng/mL on the trigger day. No more than 2 embryos will be transferred per transfer. Among participants receiving embryo transfer, LPS will be administrated until 10 weeks of gestation, with an intramuscular P4 injection of 40 mg per day or vaginal P4 (8% Crinone, Merck Serono, Switzerland) 90 mg per day, plus dydrogesterone tablet (Duphaston, Abbott, Hoofddorp, Netherlands) 30 mg per day. The LPS will be discontinued if the pregnancy failure has been confirmed by the serum pregnancy test or ultrasound assessment.

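### Per-embryo rates are to be tested with methods that treat embryos from the same woman as independent, so a chi-square P value is too small and its interval too narrow

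*Protocol article*

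**What the plan says.** Randomisation is by woman (protocol article, section 2.6): "All participants will be randomly assigned to either the EZTG group or the placebo group in a 1:1 ratio".

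Section 2.8.1 defines two secondary outcomes with the embryo as the unit:

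- "Good quality embryos rate per embryo"
- "Embryo implantation rate per embryo, defined as the number of gestation sacs detected divided by the number of embryos transferred"

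The same list counts clinical pregnancy, early miscarriage and cumulative live birth per patient, and cancellation per stimulation cycle. The choice of embryo as unit therefore looks deliberate.

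A woman can contribute several embryos to the first rate. For the second, section 2.7.4 sets a limit per transfer, not per woman: "No more than 2 embryos will be transferred per transfer".

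The analysis paragraph (section 2.9.2) covers the primary outcome "as well as other secondary outcomes". Its list of tests is: "T-test, Wilcoxon rank-sum test, or chi-square test will be used to test for differences". On summaries it says: "The results will be given as mean (standard deviation), median (interquartile range), or frequency (percentage) according to the type and distribution of the variables". The article names no method that allows for correlation within a woman, and no per-woman summary of the two embryo rates.

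**The concern.** The chi-square test takes each unit as an independent observation. Embryos from one woman are not independent: they share her age, her oocyte quality, the partner, the stimulation and the laboratory, and two embryos in one transfer share a uterus. With positive correlation within a woman, a test on pooled embryos uses a standard error that is too small. It rejects too often when there is no effect, and the 95% interval is too narrow. This is a variance error caused by the unit of analysis. It would remain even if every randomised woman produced an embryo.

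Embryo quality is not a marginal outcome here. The Discussion reports that, in the pilot of 100 women, more high-quality embryos was the only clinical outcome to differ statistically between the groups. A positive secondary claim on embryo quality is therefore plausible, and it would rest on the weakest test in the plan.

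**Working it through.** **1. The plan's own figure.** The only sample-size figure concerns the primary outcome. With a difference of 1 oocyte, SD 3, two-sided 5% and 90% power:

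n = 2 × (1.960 + 1.282)² × 3² / 1² ≈ 190 per group; 190 / (1 − 0.20) = 237.5, so 238, against 240 stated.

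This reproduces. The present point does not touch it, because oocytes are counted once per woman.

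**2. Formulas for the per-embryo rates.**

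- Design effect: DE = 1 + (m − 1) × ICC, where ICC is the within-woman correlation and m is the embryo-weighted mean number of embryos per woman, E[X²]/E[X].
- True type I error of a nominal 5% test: 2 × [1 − Φ(1.96/√DE)].
- Correct interval width divided by naive width: √DE.

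**3. Inputs.** From the article: SD of 3 oocytes, and 240 × 0.80 = 192 women per arm after dropout. The article gives no ICC, embryo count or event rate, so those below are assumptions.

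**4. Good-quality embryos, assumption set A.** Oocytes negative binomial with mean 3.5 and SD 3; 65% of oocytes give an embryo; 50% are of good quality; no true effect.

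- Embryos per arm: 192 × 3.5 × 0.65 ≈ 437, or about 2.3 per woman.
- Mean per woman: 3.5 × 0.65 = 2.275. Variance: 0.65² × 9 + 0.65 × 0.35 × 3.5 = 4.60. So m = (4.60 + 2.275²)/2.275 ≈ 4.3; the simulated value was 4.28, used below.

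| ICC | DE | √DE | Type I error, formula | Type I error, simulated (two runs) |
|---|---|---|---|---|
| 0.1 | 1.33 | 1.15 | 8.9% | 8.7%, 9.7% |
| 0.2 | 1.66 | 1.29 | 12.8% | 13.1%, 12.5% |
| 0.3 | 1.98 | 1.41 | 16.4% | 15.7%, 15.8% |

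The simulations were beta-binomial with 3000 to 4000 trials per setting. A woman-clustered ratio test on the same simulated data rejected in 5.8%, 4.6% and 4.9% of trials.

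**5. Good-quality embryos, assumption set B (shorter tail).** 192 women per arm; 1 to 6 embryos each, with probabilities 0.25, 0.25, 0.20, 0.15, 0.10 and 0.05; 40% good quality. Here E[X] = 2.75 and E[X²] = 9.75, so m = 9.75/2.75 = 3.55.

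| ICC | Type I error, simulated | Coverage of the naive 95% interval |
|---|---|---|
| 0.05 | 6.6% | 93% |
| 0.1 | 7.9% | 92% |
| 0.2 | 11.0% | 89% |
| 0.3 | 14.0% | 86% |
| 0.5 | 19.8% | 80% |

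**6. Implantation.** Clusters are smaller.

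- 140 women per arm, 1 or 2 embryos each, 20% implanting: 6.0%, 6.3% and 7.9% at ICC 0.1, 0.2 and 0.3.
- 150 women per arm, 40% with one embryo and 60% with two, 20% implanting: 5.9%, 6.5%, 6.8%, 7.8% and 9.3% at ICC 0.05, 0.1, 0.2, 0.3 and 0.5.

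If fresh and frozen transfers in one woman are both counted, her cluster can exceed two embryos and these figures would rise.

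**The case against.** The strongest reply has three parts.

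- **The test is inferred.** Section 2.9.2 assigns no test to any outcome. A t-test or Wilcoxon test on each woman's own proportion would be valid and is on the list, and naming a denominator does not fix a variance method. The article is also condensed, so clustering detail could properly sit in the analysis plan. It is right that chi-square is inferred. But the article does more than stay silent: it states the unit and a closed list of tests for all secondary outcomes. Taken together these point to chi-square on embryos. Per-woman proportions would change the quantity defined in section 2.8.1, so that route needs a change of text too.
- **The size rests on assumptions.** This stands. The first set has a long right tail, giving a weighted cluster size near 4.3 against a mean of 2.3; the second set gives less, and at ICC 0.05 only 6.6%. The direction does not depend on these choices so long as the within-woman correlation is positive.
- **The consequences are limited.** This also stands. Two secondary outcomes are affected, and for implantation the excess is about one percentage point at ICC 0.1 to 0.2. The pilot link is suggestive only: the Discussion does not say that the pilot result was a rate per embryo, and the pilot did not select on ovarian reserve.

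**Conclusion.** The concern holds. Followed as written, the plan compares per-embryo rates with a test that ignores clustering by woman, and the result is too optimistic for any positive within-woman correlation. For good-quality embryos, the true type I error is about 8% to 16% instead of 5% at ICC 0.1 to 0.3, across both sets of assumptions. Under the first set, the naive standard error is too small by a factor of about 1.15 to 1.4. For implantation the error is about 6% to 8% over the same range. These sizes rest on assumed correlations, embryo counts and event rates. The primary outcome, the sample size of 480 and the outcomes with one value per woman are unaffected. This should be corrected, but it does not threaten the main conclusion of the trial.

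**What to change.** Add one sentence to section 2.9.2 stating that every outcome counted per embryo is analysed with the woman as the cluster. Two suitable choices are a logistic GEE with standard errors robust to clustering by woman, and a comparison of ratios of totals with a woman-clustered variance. Either keeps the embryo-level rate of section 2.8.1. State also that the chi-square test is kept for outcomes with one value per woman: cancellation, clinical pregnancy, early miscarriage and live birth. If the investigators prefer a per-woman proportion with the Wilcoxon test, section 2.8.1 should be reworded to match, since that is a different quantity.

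The cost is a line of text. Section 2.10 already has embryology data recorded daily from retrieval to transfer, so nothing new need be collected as long as each embryo is linked to its woman. The only downside is wider intervals, which are the correct ones.
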